**Group 2**
**–** experimental (*n* = 32) – scaling and root planning + PDT + OHO (Table 1).

**Table 1 Tab1:** Timeline showing the sequence of procedures and sample collection

	Study period			
	Enrolment	Allocation	Post-allocation	Close-out
Time point	-t1	0	t1	t2–12 m after periodontal treatment
Enrolment:				
Calibration of clinical examiner	x			
Informed consent	x			
Eligibility screen	x			
Allocation		x		
Interventions:				
G1–positive control group			x	
G2–experimental group			x	
Assesments				
Anamnesis (epidemilogical data) and physical examination	x			
Periodontal clinical examination	x			x
Analysis of Oral Health Impact Profile (OHIP-14 questionaire)	x			x
Saint George’s Respiratory Questionaire–SGRQ	x			x
Quality of Life Questionaire–Bronchiectasis (QoL–B)	x			x
Spirometry	x			x

### Photodynamic therapy (PDT)

Patients of Group 2 will receive photodynamic therapy. PDT associates a photosensitizer with light source in order to reduce the microbial load. The procedures will be performed as described.Scaling and root planningApplication of methylene blue (0.005% - Chimiolux 10, DMC® – Purified water and methylene blue) with a carpule syringe and needle (with stop and without bevel) into the periodontal pockets >4 mmWait for 3 min (Betsy [19])Irradiation will be performed with red laser diode (λ = 660 nm) with an output power of 100 mW (MM Optics Twin Laser, São Paulo, SP, Brazil) in all sites around a tooth (six sites per tooth) on all teeth, lastly, 1 min irradiation scanning around each tooth.Washing abundantly with saline until complete removal of methylene blue

Every adverse effects will be related.

### Blinding

Patients of control group will receive simulation of using photodynamic therapy (PDT).

The simulation of PDT will be performed by applying methylene blue (0.005% - Chimiolux 10, DMC® – Purified water and methylene blue) with a carpule syringe and needle (with stop and without bevel) into the periodontal pockets >4 mm. Then, wait for 3 min (Betsy [19]). Irradiation will be performed with the laser (MM Optics Twin Laser, São Paulo, SP, Brazil) turned off in all sites around a tooth (six sites per tooth) on all teeth, lastly, 1 min irradiation scanning around each tooth. Than, the operator will wash abundantly with saline until complete removal of methylene blue.

### Statistical analysis

The Liliefors test will assess the normality of the data. If the data are normal, t test (Bioestat 5.3, Pará, Brazil) will be used to compare continuous and dependent variables of Groups 1 and 2 (periodontal parameters). If the data do not have normal distribution, Mann Whitney test will be used. Baseline data will be compared with data from 12 months after treatment. The value of *p* <0.05 will be considered statistically significant. The *x*
^2^ test will be used to compare categorical variables between Groups 1 and 2. All values will be expressed as mean ± Standard Deviation.

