### Sample size calculation

For this study, based on exacerbations of bronchiectasis, we assume that the difference between the groups will be one exacerbation with a standard deviation of 1.4 [14] with an effect size of 1. Thirty-two (32) patients per group will be necessary with a significance level of 5%, a power of 80% in a two-group t-test, using the statistical package Dell Statistica version 12.

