### Study variables

The primary variable of the study will be the number of exacerbations. Secondary variables will include spirometry (lung evaluation), dental clinical parameters (periodontal examination), and quality of life parameters (SGRQ, and OHIP-14 questionnaires). These variables will be assessed at baseline and 12 months after periodontal treatment.

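### The stated normality gate would in practice send the primary exacerbation count to Mann-Whitney, not to the t-test the trial was sized on; one pre-specified baseline-adjusted count model would be a cheap improvement

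*Protocol article*

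**What the plan says.** All references are to the protocol article.

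- **Study variables:** "The primary variable of the study will be the number of exacerbations". The section adds that the study variables are assessed at baseline and 12 months after treatment. The Abstract says exacerbation history is taken from clinical records.
- **Sample size calculation:** the assumption is that "the difference between the groups will be one exacerbation with a standard deviation of 1.4", "with an effect size of 1". The result is "Thirty-two (32) patients per group will be necessary", "with a significance level of 5%, a power of 80% in a two-group t-test".
- **Statistical analysis:** "The Liliefors test will assess the normality of the data". Normal data go to a t-test, and the only variables given as an example are periodontal ones. Then: "If the data do not have normal distribution, Mann Whitney test will be used". Categorical variables go to a chi-squared test. Baseline enters only through a comparison of baseline with 12-month data. Results are to be shown as means with standard deviations.
- **Background:** patients are said to have 6.6 exacerbations per year on average.

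No sentence in the Statistical analysis section names the exacerbation count, a count or rate model, or an adjustment for baseline.

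**The concern.** The primary outcome is an integer count. If its mean is low, its distribution is discrete and skewed, and a normality test with about 32 patients per arm will nearly always reject. The rule then replaces the t-test used for sizing with a rank test. That test is somewhat less powerful here and does not estimate what the hypothesis is about, namely fewer episodes per year. If the mean is high enough for the normality test to go either way, the data decide which test is confirmatory. In both cases the plan does not fix in advance the test on which its 80% power rests.

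The baseline count is a second matter. It is collected but not used as a covariate, so any precision it could give the between-arm comparison is lost.

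**Working it through.** **1. Reproduce the sample size.** Standardised difference = 1/1.4 = 0.714. A two-sided two-group t-test at 5% with 80% power (noncentral t) needs 31.76, so 32 per group; power at 32 is 80.3%. The stated number is right for an unadjusted t-test. (The stated effect size of 1 is not 0.714 and would need only 17 per group. That is a separate point.) There is almost no slack, so any loss from changing the test takes power below 80%.

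**2. What counts fit an SD of 1.4?** For a count with mean m and between-patient dispersion k, variance = m + k·m². The pooled SD is the root of the average of the two arm variances.
- 2.5 v 1.5, k = 0: √((2.5 + 1.5)/2) = √2 = 1.41
- 2 v 1, k = 0.15: √((2.6 + 1.15)/2) = 1.37
- 2 v 1, k = 0.3: √((3.2 + 1.3)/2) = 1.50
- 2 v 1, k = 0.6: √((4.4 + 1.6)/2) = 1.73, above the plan's figure
- 6.6 v 5.6, k = 0: √((6.6 + 5.6)/2) = 2.47, well above it

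The plan's SD therefore implies low counts.

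**3. Simulation.** Gamma-Poisson counts, 32 per arm, 1,500 trials per setting, complete follow-up. Each patient's underlying rate is shared between the baseline and follow-up years. Plan's rule: Mann-Whitney if Lilliefors p < 0.05 in either arm, otherwise the t-test. (Testing arm by arm is an assumption.) Count model: quasi-Poisson with arm, log(baseline count + 0.5) and log follow-up time as offset. The Monte Carlo standard error of one power figure is about √(0.75 × 0.25/1500) = 1.1 points.

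| Means, dispersion | Simulated SD | Normality rejected | t-test | Plan's rule | Count model, no baseline | Count model with baseline |
|---|---|---|---|---|---|---|
| 2.5 v 1.5, 0 | 1.41 | 99.9% | 80.5% | 77.6% | 80.4% | 79.2% |
| 2 v 1, 0.15 | 1.36 | 100% | 83.9% | 79.5% | 83.9% | 84.6% |
| 2 v 1, 0.3 | 1.48 | 100% | 75.8% | 70.3% | 75.8% | 79.5% |
| 6.6 v 5.6, 0 | 2.46 | 68.6% | 35.9% | 34.5% | 36.1% | 35.5% |
| 6.6 v 5.6, 0.1 | 3.12 | 65.0% | 24.4% | 24.1% | 24.3% | 27.2% |

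**4. Reading the three rows with SD 1.4 to 1.5.**
- Loss from the gate against the t-test: 80.5 − 77.6 = 2.9, 83.9 − 79.5 = 4.4 and 75.8 − 70.3 = 5.5 points.
- Gain of the full model over the rule: 79.2 − 77.6 = 1.6, 84.6 − 79.5 = 5.1 and 79.5 − 70.3 = 9.2 points.
- Part of that gain due to baseline: −1.2, +0.7 and +3.7 points. The rest comes from leaving the rank test.
- Repeat runs at these settings gave rule v model 76 v 77%, 81 v 83% and 73 v 83%, that is, gains of 1 to 10 points.

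**5. Where larger gains come from.** At 2 v 1 with dispersion 0.6 (SD about 1.7), runs gave 53 to 59% for the rule against 75 to 77% for the model. Suppose instead that 20% leave early and their counts are treated as full-year counts. The rule v model figures are then 63.2% v 75.1% (2 v 1, dispersion 0.3) and 53.0% v 67.4% (2.5 v 1.5, dispersion 0.2).

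**6. Type I error.** Under equal means, in three settings: 4.8%, 6.0% and 4.9% for the rule; 4.2%, 5.3% and 5.5% for the model.

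**7. Baseline adjustment on the plan's own figures.** Residual SD = 1.4·√(1 − ρ²), where ρ is the assumed baseline correlation. Power at 32 per arm is 80.3% at ρ = 0, 83.9% at 0.3 and 90.1% at 0.5.

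**The case against.** The strongest reply is that the gate is not explicitly assigned to the primary variable. The t-test sentence mentions only periodontal measures, and the one test tied to exacerbations is in the Sample size calculation: "a power of 80% in a two-group t-test". A fuller plan may name a primary analysis. This stands as a limit: the rule reaches the count by default, and a reader should not say the article assigns it there. It does not remove the point, because the article does fix one rule for non-categorical outcomes and that rule disagrees with the sizing.

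Other parts of the reply also stand.
- A reader might infer that patients with incomplete follow-up are discarded or counted as complete. The article does not say how they are handled. With complete follow-up, ignoring time costs nothing.
- A reader might quote a loss of 20 points or more. That needs an SD near 1.7, which the plan does not assume.
- The benefit of baseline depends on how strongly it predicts follow-up. With independent years (2 v 1, dispersion 0.3), runs gave 71% for the rule, 74% for the t-test and 73% for the adjusted model. The article supports no claim about the strength of that prediction.
- Low counts are inferred from the SD of 1.4. At 6.6 per year the gate rejects less often and no method recovers the power.
- Mann-Whitney is a valid randomised comparison, and the promised means would still show a crude difference. What is missing is a rate estimate from the test itself.

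**Conclusion.** The point holds as a cheap improvement, SHOULD-FIX. For low counts consistent with an SD of 1.4, the stated rule almost always yields Mann-Whitney. That costs about 2 to 6 power points against the t-test used for sizing and gives no exacerbation-rate estimate. At 6.6 per year the choice of test would be left to the data, with rejection in about two thirds of trials, but little power would be gained by changing method.

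With complete follow-up and SD 1.4 to 1.5, a baseline-adjusted count model gains roughly 0 to 10 points over the rule. This range rests on assumed dispersion (0 to 0.3) and on a patient rate that carries over between years; the article gives neither dispersion nor baseline correlation. Larger gains require a higher SD or assumed incomplete follow-up.

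A reader might infer that the two-stage rule inflates false positives. The simulated type I error, 4.8 to 6.0%, does not support that.

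**What to change.** Remove the normality gate for the primary variable and name one analysis. For example: the exacerbation count in all randomised patients, by quasi-Poisson regression with treatment arm, log(baseline exacerbation count + 0.5) as covariate and log follow-up time as offset, reporting the rate ratio with its 95% confidence interval. State the period the baseline count covers. Keep Mann-Whitney as a sensitivity analysis.

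Quasi-Poisson is suggested because it is the model simulated here. Negative binomial fits with one package's default settings failed to converge in about 20% of trials at dispersion 0.15 and 41% at zero dispersion, and a fallback for non-convergence would bring back a data-dependent choice.

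The cost is a change of wording and a regression package in place of the two-group tests. No visits, measurements or patients are added. Without the baseline term the count model had virtually the same power as the t-test in the low-count settings with complete follow-up, so the change gives no reason to alter the 32 per group. The downside is a model-based estimate that is slightly harder to explain.

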## Methods

A randomized, controlled, 12-month, parallel-group clinical trial, registered at www.clinicaltrial.gov (NCT02514226) will be performed. After verbal and written explanation of the study, patients will sign the Informed Consent Form approved by the Research Ethics Committee (# 1.057.901) Universidade Nove de Julho (UNINOVE). A researcher not involved in the study will enroll patients. Forty patients under medical care at InCor-FMUSP with generalized chronic periodontitis will receive periodontal treatment at Universidade Nove de Julho’s Dental Clinic, from August 2016 to September 2018.

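### The between-arm test for the continuous secondary variables leaves the collected baseline values unused, and the added baseline versus 12-month comparison has no named test and no stated role

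*Protocol article*

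**What the plan says.** The Methods section describes "A randomized, controlled, 12-month, parallel-group clinical trial". Sample size calculation assumes that "the difference between the groups will be one exacerbation with a standard deviation of 1.4" and uses a two-group t-test, so the design rests on a contrast between arms.

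Statistical analysis gives these rules:

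- For normally distributed data, the t test "will be used to compare continuous and dependent variables of Groups 1 and 2 (periodontal parameters"; the bracket closes after those words and lists nothing else.
- "If the data do not have normal distribution, Mann Whitney test will be used".
- For categorical data, the chi-square "test will be used to compare categorical variables between Groups 1 and 2".
- "Baseline data will be compared with data from 12 months after treatment". No test is attached to this sentence. It does not say whether the comparison is within each arm, pooled, or of change between arms, or whether it is descriptive or inferential. The general threshold of p < 0.05 follows directly.

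Under Study variables, "The primary variable of the study will be the number of exacerbations"; spirometry, periodontal parameters, SGRQ and OHIP-14 are secondary. The section adds: "These variables will be assessed at baseline and 12 months after periodontal treatment". Table 1 shows the same two time points for these secondary variables.

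**The concern.** There are two linked weaknesses.

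**Unused baseline.** Each continuous secondary variable is measured twice in the same patient, and the stated between-arm test uses no baseline value. With variables that tend to be stable within a patient, this gives up precision already paid for.

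**A comparison without a role.** A baseline versus 12-month comparison stands beside the between-arm tests under the same significance threshold. It does not estimate the effect of treatment, and three features of this trial could produce improvement in both arms:

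- The control arm receives oral hygiene orientation and supragingival treatment (Randomization), and Table 1 calls it a positive control.
- Patients are seen every 3 months for motivation and hygiene control (section on strategies for enrolment).
- Patients are selected partly on probing depth (Inclusion and exclusion criteria), which is also an outcome, so some regression to the mean is to be expected.

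The article's aims speak of improvement after 1 year. A significant change in the experimental arm alone could therefore be reported as benefit although the arms had not been shown to differ.

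**Working it through.** **1. The plan's own figure.** Inputs from Sample size calculation: difference 1, SD 1.4, 5% level, 80% power, two-group t-test. Sidedness is not stated; two-sided is used here.

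- Standardised difference: 1/1.4 = 0.714.
- Normal approximation: 2 × (1.960 + 0.842)² × 1.4² / 1² = 30.8, so 31 per group.
- Noncentral t: 31.76, so 32 per group, with power 80.3% at 32.

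The stated 32 per group is reproduced. It belongs to an unadjusted comparison between arms.

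**2. Precision lost by leaving out baseline.** Let r be the correlation between a patient's baseline and 12-month values. The article does not give it, so a range is assumed. Relative to the unadjusted 12-month comparison, the variance is 1 − r² for ANCOVA and 2(1 − r) for change scores compared between arms.

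| r (assumed) | ANCOVA, 1 − r² | Equivalent gain in patients, 1/(1 − r²) | Change score, 2(1 − r) |
|---|---|---|---|
| 0.3 | 0.91 | 1.10 | 1.40 |
| 0.5 | 0.75 | 1.33 | 1.00 |
| 0.7 | 0.51 | 1.96 | 0.60 |

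The article states no target difference for the secondary variables. As an illustration only, take the same standardised difference of 0.714 with 32 per arm. Power is then 80% unadjusted, and 84%, 90% and 98% with ANCOVA at the three correlations. The n per arm needed for 80% power falls from 32 to 29, 25 and 17. The adjustment does not call for a larger sample.

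**3. Risk in reading before-after results as efficacy.** Suppose both arms truly change by the same amount and each within-arm test has power p. The arms are independent, so:

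P(significant in the experimental arm only) = p(1 − p)

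- p = 0.8: 0.8 × 0.2 = 16%
- p = 0.5: 0.5 × 0.5 = 25%, the maximum

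**4. Check by simulation.** 20,000 trials, 32 per arm, normal data, SD 1.4, no treatment effect, and both arms improving by an assumed 0.5 or 1 unit, with r from 0.3 to 0.7.

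| Test | Significant, shift 0.5 | Significant, shift 1 |
|---|---|---|
| Paired before-after, experimental arm | 38–72% | 91–99.9% |
| Between arms at 12 months | about 5% | about 5% |

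The between-arm test keeps its level. The before-after test detects the shared improvement, which says nothing about the treatment.

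**The case against.** The strongest reply is that the randomised contrast is planned. The t test and chi-square are stated for Groups 1 and 2, and the sample size rests on a difference between groups. That stands: a reader might infer that the before-after comparison replaces the comparison of arms, and the article does not support this.

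Other stronger readings also fail:

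- **Unpaired tests applied to paired values.** A reader might infer this because no other test is named, but the article attaches no test to that sentence. If it were done with positively correlated values, the error would be conservative: with no change at all, the simulation rejects in 0.1–1.8% of trials instead of 5%.
- **Lack of adjustment creates bias.** It does not. The unadjusted comparison is valid and costs only precision.
- **A larger misreading risk.** The chance that exactly one arm is significant, in either direction, is 2p(1 − p), or 32% and 50%. A false claim of benefit needs the experimental arm alone, which halves these figures.

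It is also fair to say that the article contains no rule that turns a within-arm result into an efficacy claim, that the sentence could mean change compared between arms, and that covariates are often left to a fuller document. On the change-score reading the comparison would be randomised, but still less efficient than ANCOVA and, at r = 0.3, worse than no adjustment. As for a fuller document, the point rests on what the article states: an unadjusted test, and a further comparison that can be read in several ways under a p < 0.05 threshold.

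Finally, the change below does not settle the analysis of the primary variable, whose test the Statistical analysis section does not name expressly. That is correct and is a separate matter.

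**Conclusion.** The point holds as an improvement that costs nothing but wording; it is not a flaw that invalidates the trial. The planned between-arm test is sound, but gives up 9%, 25% or 49% of the variance at assumed correlations of 0.3, 0.5 and 0.7. The gain is small at the low end and substantial at the high end. The ratios are the usual large-sample ones and assume a linear relation with similar variance at both times.

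The baseline versus 12-month comparison should carry no efficacy claim. If both arms change equally, it would favour the experimental arm alone with probability 16% at 80% within-arm power and 25% at 50%. This is the size of a possible misreading, not of an error that the article commits.

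**What to change.** Replace the baseline versus 12-month sentence in Statistical analysis with:

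> Each continuous secondary variable at 12 months will be compared between groups by ANCOVA with treatment arm and the patient's baseline value as covariate, reporting the adjusted mean difference with 95% CI; within-group changes from baseline are descriptive and are not tested.

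For consistency, state that this takes the place of the t test or Mann-Whitney choice for these variables, and that it covers spirometry, SGRQ and OHIP-14 as well as the periodontal parameters named in the bracket.

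The cost is analysis wording only. The baseline values are already scheduled, and no visit, measurement or patient is added.

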### Study variables

The primary variable of the study will be the number of exacerbations. Secondary variables will include spirometry (lung evaluation), dental clinical parameters (periodontal examination), and quality of life parameters (SGRQ, and OHIP-14 questionnaires). These variables will be assessed at baseline and 12 months after periodontal treatment.

### Strategies for achieving adequate participant enrolment to reach target sample size

Patients will be evaluated every 3 months in order to motivate and hygiene control.

## Discussion

Lung diseases, such as chronic obstructive pulmonary disease (COPD) and bronchiectasis, cause impairment to a patient’s quality of life with large numbers of comorbidities. It has been shown that periodontal treatment (PT) and oral hygiene (OH) deceases the severity of COPD [4]; but, despite clinical and pathophysiological similarities between COPD and bronchiectasis [20], there is no study to date about the relationship of bronchiectasis with periodontal disease (PD). Patients with bronchiectasis have multiple episodes of disease exacerbations. Interventions, such as physical exercises and chronic administration of certain drugs decrease the number of such occurrences, but no intervention can achieve results within less than 6 months [21–30]. In this study, we will perform an oral intervention with a 1-year follow up. We will measure the number of exacerbations, spirometry data, dental clinical parameters and quality of life parameters (SGRQ, and OHIP-14 questionnaires). *Saint George’s Respiratory Questionnaire* is the most complete instrument, considered the gold standard for lung diseases, and OHIP-14, which analyze the impact of oral health profile. It is expected that periodontal treatment maintained for 1 year will help reduce the number of exacerbations, improve lung mechanics and quality of life in bronchiectasis patients.

## Abbreviations

COPD: Chronic obstructive pulmonary disease
FEV1: forced expiratory volume in one second timed
FVC: Forced vital capacity
OH: Oral hygiene
PD: Periodontal disease
PDT: Photodynamic therapy
PT: Periodontal treatment
SGRQ: *Saint George’s Respiratory Questionnaire*
